### 2.3. Subject Enrollment

#### 2.3.1. Eligible Household Selection

For each of the 77 selected medium or high traffic airports, the FAA generated 40, 45, 50, and 55 dB *L*_night_ contours based on 2018 traffic to and from the associated 202 runway ends that averaged at least one departure or arrival per hour between 10:00 p.m. and 6:59 a.m. (Figure 2). The shape (.shp) files of the contours were used to determine which census blocks were within (or partially within) the outermost noise contour (i.e., 40 dB *L*_night_). Residential addresses associated with the identified census blocks were obtained based on the Computerized Delivery Sequence File from the United States Postal Service. These addresses were geocoded to the appropriate noise strata. Geographic information systems (GIS) software was utilized to assign latitude and longitude to all addresses that fall within the outermost noise contour. Addresses falling outside of the outermost noise contour were excluded from the sampling frame (zero useable addresses were available within the noise contours of one airport). For the remaining addresses, we determined which of the four noise strata each address belonged to (i.e., 40 < 45, 45 < 50, 50 < 55, ≥55 dB *L*_night_) and 308 sampling cells were created by crossing the four noise strata with the 77 airports.

The sampling target for each sampling cell is proportional to the population within the sampling cell relative to the total population of all sampling cells in each noise stratum. A random sample of addresses is sampled within the 308 sampling cells based on the sampling targets identified (those around PHL and ATL who have already participated in the pilot study are ineligible to participate again in the NSS). Based on response rates observed in the pilot study around ATL, an 88% delivery rate for mailed Recruitment Surveys, a 21% response rate among deliverable surveys, and a 9% participation rate among completed surveys was expected. Thus, it was anticipated that 24,500 surveys needed to be mailed to recruit 400 participants into the in-home sleep study. For each of the four strata 6125 addresses were selected. In addition, a reserve sample of 19,980 addresses was sampled, for a total of 44,480 addresses, to allow for lower response rates than anticipated.

#### 2.3.2. Participant Recruitment

Due to the constraints of available in-home monitoring equipment and to investigate participants across the whole year, the sample is fielded over a 24-month period with a new randomly assigned subset of the sample released every month. Each round contains approximately 1/24 of the total sample with each noise stratum equally represented in each round. The first Recruitment Survey wave was sent out in September 2021 and the last wave was sent out in August 2023. Sample sizes are adjusted each month based on the accumulated response pattern data to achieve similar sample in-home study completion sizes in each of the four *L*_night_ strata.

The mailing protocol follows procedures outlined by Dillman et al. [30] which were tested in a previous pilot study [31]. The Recruitment Survey consists of 25 questions (see Appendix A) that were chosen to maximize response rates and minimize the burden on the respondent, while providing information necessary to determine field-study eligibility and generate sampling weights (see Section 2.3.3 and Section 3.3.4). All sampled addresses are contacted between 2 and 4 times, depending on when the questionnaire is returned. The materials are addressed to “<city> resident”. For the initial survey wave, respondents can only return the paper version of the survey in the pre-paid envelope. A thank-you/reminder postcard is sent out 7 days after the initial survey mailing. Only non-respondents to prior mail packages receive subsequent survey package mailings. Mailings returned as postal non-deliverable (PND) are excluded from subsequent mailings. If no response is received three weeks after the initial survey was sent out, a second Recruitment Survey is sent out. In the follow-up rounds, respondents can complete the survey either by mail or online; providing multiple response modes is an effective method to improve overall survey response [30]. If no response is received six weeks after the initial survey was mailed, a third and final Recruitment Survey is sent out. The survey mailing number (1, 2, or 3) will be indicated on the survey and represented in the dataset.

The contents of each survey packet include a cover letter, a brief overview of the field study, a paper questionnaire that the respondent is asked to return via an included postage-paid envelope or completed online (in the second and third mailing only), a USD 2 cash incentive (first packet only) [31], and a slip in Spanish that asks respondents who only speak Spanish to request a Spanish survey packet via telephone. A URL to a study web site at the University of Pennsylvania (UPenn) is provided for respondents who want to learn more about the field study, together with a telephone number by which the study team can be reached. One individual per household is randomly sampled to complete the survey using the Last Birthday Method. The instructions on the first page of the survey will ask the adult who most recently celebrated a birthday to fill out the questionnaire. Westat scans, verifies, cleans, harmonizes, and dispositions the paper and web Recruitment Survey data and securely delivers new respondent data to UPenn weekly. Survey respondents who indicated their interest in participating in the in-home study on the survey are contacted by the UPenn research team following the algorithm outlined in Figure 3.

If a respondent is both interested in participating in the study and meets the eligibility criteria (see Section 2.3.3), the respondent is contacted via telephone following standardized telephone scripts to verify eligibility and gain consent according to Institutional Review Board (IRB) regulations (if respondents do not provide a telephone number this will be solicited through either email or standard mail). There are minimal risks associated with taking part in the field study, which are described to interested respondents and explicitly stated in the informed consent form (ICF). Prospective participants are given ample time to read the ICF and contact the study team with any questions regarding the information provided in the ICF. If respondents decide to participate in the field study after review of the ICF, they can sign the ICF electronically. Alternatively, a paper version can be mailed by the study team. Once subject consent is received, staff members call to schedule the individual for participation in the field study (see Section 2.4).

#### 2.3.3. Eligibility Criteria

To be eligible to participate in the in-home study, participants must have completed the Recruitment Survey. Survey respondents interested in participating in the in-home sleep study are ineligible to participate if they (1) are less than 21 years of age (Recruitment Surveys received from individuals under 21 years of age are discarded); (2) have a Body Mass Index (BMI; calculated based on self-reported height and weight information) greater than 35 kgm^−2^ or less than 17 kgm^−2^; (3) have been diagnosed with a sleep disorder, including obstructive or central sleep apnea, narcolepsy, restless legs syndrome, or periodic limb movement syndrome; (4) frequently (3 or more times per week) use prescription or over the counter medication to aid sleep; (5) have a hearing impairment; (6) have a cardiac arrhythmia; (7) work night shifts (defined as working for at least 4 h between 12 a.m. to 6 a.m.); (8) have dependents that frequently require care during the night; (9) are pregnant; (10) participated in the ATL and PHL pilot studies; or (11) do not habitually use earplugs or play back sounds in the bedroom that could mask aircraft noise.

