### 2.2. Sample Size and Power Calculations

#### 2.2.1. Primary Outcome and Assumptions

The primary outcome of aircraft noise-induced awakening probability is obtained using an estimated exposure–response function that describes the relationship between the *L*_AS,max_ of an aircraft overflight measured inside the bedroom and the probability of awakening determined by changes in heart rate and body movement.

During data analysis, a certain window after the start of an aircraft noise event is screened for an awakening from sleep. The duration of this window is critical (see Brink et al. [28]). If the window is too short, noise-induced awakenings may be missed. If it is too long, awakenings unrelated to aircraft noise may be picked up. For the analyses presented below, we used a screening window from 5 s before until 45 s after the start of an ANE, for a total length of 50 s for each noise event. These durations were shown to maximize signal-to-noise ratio in the pilot studies [23,24]. The screening window is extended to five seconds prior to the start of the ANE to account for uncertainties in the correction of the relative time drift between the sound recorder and the Faros ECG monitor (see Section 2.4.2).

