#### 2.4.1. Field Study Data Collection Procedures

A sound recorder, an ECG and movement monitor, and a printed manual are mailed to participants in the week prior to their scheduled start date. The manual contains (1) detailed instructions for setting up, breaking down, and mailing back the equipment; (2) step-by-step procedures to follow each night and morning of the study; (3) a Characteristics Questionnaire to be filled out once prior to the first study night (see below); and (4) Morning Surveys to be filled out each morning after waking. The manual also contains links to instructional videos with step-by-step explanations of equipment setup and study procedures.

Participants are instructed to adhere to their usual bedtimes. During the measurement period, they start and stop acoustic and physiologic measurements before they go to bed and after they get up, respectively. Sounds, ECG, and body movements are continuously recorded during this measurement period. Participants are instructed to turn off any TVs, radios, music, or sound machines before going to bed and not to wear ear plugs or headphones during the night. They are told to leave central or window air conditioning units or fans that keep them comfortable during the night on, but to place moveable fans as far away from the sound recorder as possible.

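### Item 11 of the ineligibility list is printed with reversed polarity: it excludes people who sleep without earplugs or masking sound

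*Protocol article*

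**What the plan says.** Section 2.3.3 of the protocol article gives one numbered list of eleven conditions under the lead-in "Survey respondents interested in participating in the in-home sleep study are ineligible to participate if they". The items are reasons for exclusion, and meeting any one is enough. Typical entries are item 5, "have a hearing impairment", and item 10, "participated in the ATL and PHL pilot studies". Item 11 reads "do not habitually use earplugs or play back sounds in the bedroom that could mask aircraft noise".

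Four other places bear on it:

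- Section 2.4.1 tells participants to "turn off any TVs, radios, music, or sound machines before going to bed" and "not to wear ear plugs or headphones during the night".
- Section 2.2.1 defines the primary outcome through the maximum level "of an aircraft overflight measured inside the bedroom and the probability of awakening determined by changes in heart rate and body movement".
- Section 2.1.2 makes meeting the eligibility criteria part of the definition of the target population.
- Section 3.3.4 adjusts the weights for eligibility at successive steps, including the telephone screening questions. The final weights are meant to add up to the number of people who could be eligible in each stratum.

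**The concern.** The negation in item 11 sits inside a list that is already negative. Read literally, the double negative turns the rule round: people who sleep without acoustic protection are refused, and those who habitually protect themselves are not.

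This is not background text. It helps to define the population to which the exposure–response function applies, and it is an input to the weights. If it were followed as printed, participants would be people used to sleeping with noise reduced or masked, then told to stop for five nights. Their awakening probability at a given bedroom level would be observed in an unaccustomed condition. It would not describe residents who normally sleep unprotected, although Section 1.4 claims national representativeness.

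**Working it through.** No arithmetic applies. The check is to read the sentence as a logical rule and compare it with the rest of the article.

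**Step 1. The rule.** A respondent is ineligible if (1) or (2) or … or (11) is true. Let E mean habitual use of earplugs and S mean habitual playing of masking sound. Item 11 can be parsed in two ways:

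- Natural parse, with *do not* governing both verbs: item 11 = NOT (E or S).
- Narrower parse, with *do not* governing only the earplug clause: item 11 = (NOT E) or S.

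**Step 2. Truth table.** This shows the effect of item 11 alone; items 1 to 10 still apply.

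| Habit | Natural parse | Narrower parse | With *do not* deleted (E or S) |
|---|---|---|---|
| Neither | ineligible | ineligible | not excluded |
| Earplugs only | not excluded | not excluded | ineligible |
| Masking sound only | not excluded | ineligible | ineligible |
| Both | not excluded | ineligible | ineligible |

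The first two rows are the same under both parses: a person who uses neither is refused, and a person who uses only earplugs is not. The earplug condition is therefore reversed either way. The masking-sound condition is reversed only under the natural parse.

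**Step 3. Comparison with items 1 to 10.** Each of the other ten items states directly the feature that disqualifies. Item 11 is the only one phrased as something a suitable participant would satisfy. That pattern suggests an inclusion-style phrase placed in an exclusion list.

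**Step 4. Comparison with the field procedure.** Section 2.4.1 removes earplugs, headphones and sound machines on study nights, while the same section says "Participants are instructed to adhere to their usual bedtimes". A sample accustomed to sleeping without masking fits those instructions; a sample of habitual maskers fits them poorly. No section gives a reason for restricting the study to habitual maskers.

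**Step 5. Can the intended direction be confirmed elsewhere?** None of the 25 Recruitment Survey questions in Appendix A asks about earplugs or masking sound, so no survey item settles it. Section 2.3.2 describes scripted telephone calls to verify eligibility. The scripts are not shown, and neither is the content of Figure 3 (the enrolment process). The Characteristics Questionnaire in Section 2.4.1 asks about noise countermeasures and may offer a check on who was enrolled.

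**The case against.** The strongest reply is that this is a drafting slip whose intent any reader can recover from the other ten items, and that nobody chose to enrol only earplug users. That is very probably right. It does not remove the point, because an eligibility criterion that helps to define the population and feeds the weights should not have to be read as its opposite.

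Several further objections stand and limit the finding:

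- **Conduct.** A reader might infer that the enrolled sample consists of habitual maskers. The documents do not support this. The article condenses a fuller protocol, the telephone scripts are not shown, and no section reports screening in the printed direction.
- **Contradiction.** A reader might say that item 11 flatly contradicts Section 2.4.1. It does not. Item 11 concerns habit and Section 2.4.1 concerns behaviour on study nights. Enrolling habitual users and asking them to stop would be odd but logically possible. The field instructions indicate intent; the lead-in and the polarity of items 1 to 10 are the firm evidence.
- **Survey.** The absence of an earplug question is not a defect in itself. Pregnancy and pilot participation are also absent from Appendix A, and telephone verification is the described procedure.
- **Weights.** Harm to the weights requires an eligibility flag coded from the printed text. Nothing suggests that this happened.
- **Timing.** At writing, 385 of the planned 400 participants had been measured, so a correction cannot change who most of them are. The two-year analysis period was still ahead, however, and the weights and the population statement could still be put right.

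**Conclusion.** The point holds for the printed text. Item 11 excludes people who use neither earplugs nor masking sound under either parse; on the natural parse it leaves only habitual users eligible, subject to items 1 to 10. It is inconsistent with the polarity of items 1 to 10 and fits poorly with the instructions for study nights.

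The size is qualitative. Taken literally, the rule replaces the intended population with its complement on this characteristic. The article gives no prevalence of earplug or masking-sound use, so neither the share of residents affected nor a shift in the exposure–response function can be calculated. Any bias in the data is conditional on the text having been applied as written, for which there is no evidence. What is established is a wrongly stated eligibility rule, and with it a wrongly stated population.

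**What to change.** Delete *do not* from item 11, so that habitual use of earplugs or of masking sound becomes the excluding condition, in line with items 1 to 10.

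Before the weighted analysis, confirm that the telephone screening script and the eligibility flag used in the Section 3.3.4 weighting steps run in that direction. If the countermeasure answers in the Characteristics Questionnaire cover earplugs and masking sound, tabulate them for enrolled participants as a direct check. If the script or flag turns out to have followed the printed wording, report that and describe the population accordingly.

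The cost is two words and a short check of existing records. No new data and no change to the sample size or the model are needed.

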### 2.4. Field Study

The research team at UPenn is responsible for performing the field study, which is conducted year-round except for the week of Thanksgiving, the week of Christmas, and the weeks preceding and following Christmas (i.e., for 48 weeks of the year). On average, four participants are investigated per week to meet the total recruitment goal of N = 400 participants over a two-year period; although, more or fewer subjects may be investigated in any given week based on participant availability. The first participants were investigated in early October 2021 and the field study is expected to end in October 2023. Subjects participate in the field study for five consecutive nights/mornings starting on a Monday night and ending on the following Saturday morning. The weekend period was excluded as traffic volume typically decreases on weekend nights.

#### 2.4.1. Field Study Data Collection Procedures

A sound recorder, an ECG and movement monitor, and a printed manual are mailed to participants in the week prior to their scheduled start date. The manual contains (1) detailed instructions for setting up, breaking down, and mailing back the equipment; (2) step-by-step procedures to follow each night and morning of the study; (3) a Characteristics Questionnaire to be filled out once prior to the first study night (see below); and (4) Morning Surveys to be filled out each morning after waking. The manual also contains links to instructional videos with step-by-step explanations of equipment setup and study procedures.

Participants are instructed to adhere to their usual bedtimes. During the measurement period, they start and stop acoustic and physiologic measurements before they go to bed and after they get up, respectively. Sounds, ECG, and body movements are continuously recorded during this measurement period. Participants are instructed to turn off any TVs, radios, music, or sound machines before going to bed and not to wear ear plugs or headphones during the night. They are told to leave central or window air conditioning units or fans that keep them comfortable during the night on, but to place moveable fans as far away from the sound recorder as possible.

Each morning after waking the participants complete the Morning Survey, which is embedded in the manual sent to participants. The Morning Survey has questions on alcohol and caffeine consumption in the 6 h pre-bed; how stressful the last day was; whether the bedroom window was closed, partially open, or completely open during the night; whether the bed was shared; lights out time, wake time, rise time, sleep latency (defined as the time it takes to fall asleep), and the number of awakenings; tiredness, sleep quality, and sleep disturbance due to aircraft noise. It also assesses sleepiness with the Karolinska Sleepiness Scale [32] and allows participants to leave general comments at the end. It takes less than five minutes to complete the Morning Survey. After completing the Morning Survey, participants go about their normal daily and evening activities. Subjects can contact the study team through email and/or phone. Staff members are available around the clock via cell phone to answer any questions or concerns about equipment or procedures. The research team always calls participants on the first night and last day of their measurement period to answer any questions.

Participants also fill out the Characteristics Questionnaire prior to the first study night. The purpose of this questionnaire is to obtain additional information on field study participants that may affect or explain how they physiologically respond to the aircraft noise exposure. The Characteristics Questionnaire takes approximately 15 min to complete and includes:Morningness–Eveningness Questionnaire (MEQ), a standardized method of measuring chronotype [33];Pittsburgh Sleep Quality Index (PSQI), a standardized method of measuring sleep quality over the past month [34];Noise Sensitivity Questionnaire (NoiseQ), reduced version, a standardized method for measuring sensitivity to noise [35,36]; andAdditional questions considered relevant but not included in the Recruitment Survey. The questions address noise countermeasures; sleep disturbance by road, rail, industry, construction, neighbors, and air conditioning over the past 12 months; whether the residence received sound proofing treatment; and whether participants use air conditioning in their bedroom. Questions on sleep disturbance are formulated according to standard guidelines described by the International Commission on the Biological Effects of Noise (ICBEN) [37].

After the last study night, participants follow instructions provided in the manual for breaking down and packing away the equipment and the manual, which they then ship back to the research team. After receiving the equipment at UPenn, participant data are backed-up and the equipment is cleaned, disinfected, tested for nominal operation, and then prepared for the next participant by the research team.

#### 2.4.2. Field Study Equipment

The sound recorder and ECG/movement device are the main field study components. The materials sent to study participants also include protective foam, the manual, chargers and an extension cord, ECG electrodes (electrodes from two different brands are included in case a participant has an allergic reaction to the standard electrodes), disinfectant and adhesive removal wipes, as well as a corticosteroid cream, for skin preparation/care, tape and a return shipping label, and a payment form and Debit card (ClinCard). Most of these components are stored in labeled Ziploc bags (Figure 4C).

